### Patient Eligibility

Relevant to STTEPP, PROCEED study participants are divided into subcohorts to distinguish the natural history of different disease presentations at the time of admission into the cohort [34]. In STTEPP, we will leverage the resources of the CPDPC by approaching participants already enrolled in PROCEED. This approach will facilitate timely accrual, as these participants have demonstrated an interest in research and willingness to participate in CPDPC studies. Although all participants must meet the criteria for diagnosis of suspected or definite CP as per PROCEED definitions [34], study enrollment will not be limited to participants participating in PROCEED. The STTEPP inclusion and exclusion criteria are listed in Textboxes 4 and 5, respectively.

Inclusion criteria.Written informed consent and Health Insurance Portability and Accountability Act (HIPAA) authorization for release of personal health informationAge ≥18 years at the time of informed consentSuspected (YELLOW 2 or 3) or definite (RED) diagnosis of chronic pancreatitis, as per the Consortium for the Study of Chronic Pancreatitis, Diabetes, and Pancreatic Cancer’s *Prospective Evaluation of Chronic Pancreatitis for Epidemiologic and Translational Studies* (PROCEED) study definition with ongoing symptoms of abdominal painPatients must be maintained on an opioid (except methadone or suboxone) for 4 weeks before enrollment for the treatment of abdominal pain related to pancreatitis, with a daily morphine equivalent dose of 20 mg to 120 mg.Ongoing symptoms of abdominal pain even with opioid use (Visual Analog Score and Brief Pain Inventory average score ≥4, at enrollment)Eastern Cooperative Oncology Group performance status of 0 to 2 (Oken et al [35])Ability to swallow and tolerate oral tabletsFemales of childbearing potential must have a negative pregnancy testThe following laboratory parameters must be met: white blood cell count ≥3.0 K/mm^3^, absolute neutrophil count ≥1.5 K/mm^3^, hemoglobin ≥9 g/100 ml, platelets ≥75 K/mm^3^, creatinine ≤1.5 mg/100 mL, bilirubin ≤1.5 x upper limit of normal (ULN), aspartate transaminase ≤3 ULN, alanine transaminase ≤3 ULN; normal PR interval on baseline 12-lead electrocardiogram.

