Exclusion criteria.Participants with indeterminate chronic pancreatitis (YELLOW 1) as per *Prospective Evaluation of Chronic Pancreatitis for Epidemiologic and Translational Studies* (PROCEED) criteriaTreatment with any investigational agent within 30 days before registration or concurrent participation in a clinical trial which involves another investigational agentRapidly escalating pain that requires parenteral (eg, intravenous or intramuscular) opioid therapy within 30 days of enrollmentKnown hypersensitivity or allergic reaction to lacosamide, carbamazepine, or oxcarbazepinePregnant or breastfeedingDiagnosis of epilepsy or a patient who is currently taking antiepileptic drugsAbdominal surgery or pain intervention (eg, endoscopic retrograde cholangiopancreatography with sphincterotomy or stent or stone removal and celiac plexus block) within 90 days of enrollment.Hospitalization for pancreatitis exacerbation or pain management within 90 days of enrollmentPatient who currently takes Suboxone or methadone.Other factors which might explain the patient’s ongoing symptoms, at the discretion of the enrolling physician.History of autoimmune or traumatic pancreatitis or sentinel attack of acute necrotizing pancreatitis which results in suspected disconnected duct syndrome.Primary pancreatic tumors, pancreatic ductal adenocarcinoma, suspected cystic neoplasm (>1 cm in size or main duct involvement), neuroendocrine tumors, and other uncommon tumorsPancreatic metastasis from other malignanciesHistory of solid organ transplant and HIV or AIDSKnown isolated pancreatic exocrine insufficiency (eg, without any eligible inclusion criteria)No medical or psychiatric illnesses or ongoing substance abuse that, in the investigator’s opinion, would compromise participant’s ability to tolerate study interventions or participate in follow-up.

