### Investigational Plan, Intervention, and Treatment Regimen

We will conduct a dose-escalation trial of lacosamide added to opioid therapy in patients with chronic abdominal pain owing to CP. Participants who meet all the inclusion criteria and none of the exclusion criteria will be included in this dose-finding study. We will use the Bayesian optimal interval (BOIN) [37,38] design to determine the MTD. The BOIN design received a fit-for-purpose designation from the FDA as a drug development tool [39]. The BOIN design is implemented in a simple manner similar to the traditional 3+3 design, but it is more flexible and possesses superior operating characteristics compared to those with more complex model-based designs, such as the continual reassessment method [40]. The target DLT rate for MTD is 0.3, and the maximum sample size is 24. We will enroll and treat patients in cohorts of size 3. The initial dose will be 50 mg taken orally twice a day (100 mg/day), followed by an incremental increase of 100 mg/day in 2 divided doses. The maximum daily dose of lacosamide will be 400 mg/day. The duration of lacosamide administration will be 7 days at each dose level. This target DLT rate and dose-escalation schedule were chosen based on previous trials that had suggested the efficacy and tolerability of comparable doses of lacosamide when used to treat partial seizures and painful diabetic neuropathy. Follow-up laboratory parameters (as obtained at study entry) will be obtained on day 8 (with a 3-day window) after therapy is completed. The trial design is illustrated in Figure 1 and is described as follows:

Patients in the first cohort are treated at dose level 1.To assign a dose to the next cohort of patients, dose escalation or de-escalation will be performed according to the rules displayed in Table 1.Repeat step 2 until the maximum sample size of 24 is reached or stop the trial if the number of patients treated at the current dose reaches 15.

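### The last exclusion criterion is worded as an inclusion requirement, so its literal effect reverses its evident intent

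*Protocol article*

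**What the plan says.** Under Patient Eligibility, the protocol article states that "The STTEPP inclusion and exclusion criteria are listed in Textboxes 4 and 5, respectively". Textbox 5 opens with "Exclusion criteria.Participants with indeterminate chronic pancreatitis (YELLOW 1" and is therefore the exclusion list. Its last item begins "No medical or psychiatric illnesses or ongoing substance abuse that" and goes on, subject to the investigator's opinion, to describe conditions that "would compromise participant’s ability to tolerate study interventions or participate in follow-up".

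The rule for using the two lists is in the section on the investigational plan, intervention and treatment regimen: "Participants who meet all the inclusion criteria and none of the exclusion criteria will be included in this dose-finding study".

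**The concern.** A criterion that begins with 'No' describes a person who is suitable. That is the form of an inclusion requirement, but here it stands among the exclusions, none of which may be met. The two negatives combine so that the literal rule points the wrong way.

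This is operative eligibility text, not background. The item is also the only one in either list that names psychiatric illness or ongoing substance abuse. All participants take opioids, and the Introduction counts overdose and opioid use disorder among the serious risks of opioid use. The item also screens for ability to tolerate the intervention and attend follow-up, which bears on two of the trial's stated end points: tolerability (judged by compliance) and feasibility (judged partly by dropout).

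**Working it through.** No figure is involved. The check applies the stated rule to the stated item.

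**Inputs**
- Item: no compromising illness or substance abuse (Textbox 5, last item).
- List: exclusion (Patient Eligibility assigns Textbox 5 to exclusions).
- Rule: enter only if every inclusion criterion is met and no exclusion criterion is met (Investigational Plan).

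**Literal result for this item alone, and the result under each repair**

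| Person | As printed | 'No' deleted, kept as exclusion | Sentence moved unchanged to inclusion |
|---|---|---|---|
| Has no such condition | Statement true, exclusion met: barred | Exclusion not met: not barred | Inclusion met: not barred |
| Has such a condition | Statement false, exclusion not met: not barred by this item | Exclusion met: barred | Inclusion not met: barred |

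The printed column is the reverse of the other two in both rows. The two repairs give identical decisions.

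**Is the wording a convention of the list?** No. Textbox 5 has 16 items. The other 15 each name the thing that excludes, such as pregnancy, known hypersensitivity to the drug or current methadone use. Only the last is framed as an absence.

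**Is it a defect of the text extraction?** Nothing suggests so. The sentence is complete and shows no gap or redaction.

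**Does another item repair it?** Not for psychiatric illness or substance abuse, which neither textbox mentions elsewhere. For general medical fitness, partly:
- Textbox 4 requires performance status 0 to 2, limits on blood counts, creatinine, bilirubin and transaminases, and a normal PR interval.
- Textbox 5 excludes epilepsy or antiepileptic drug use, organ transplant and HIV or AIDS, pancreatic tumours, and recent hospitalization for pancreatitis exacerbation or pain management.

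**Does it reach the statistics?** No. The target toxicity rate of 0.3, the boundaries in Table 1, the cohort size of 3 and the maximum of 24 do not depend on this wording.

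**The case against.** The strongest reply is that no investigator could follow the literal reading. It would turn away everyone fit to take part and leave only people whom the investigator judges unable to tolerate treatment or complete follow-up. The item depends on that judgement, and nobody who made it would enrol the person because of it. This stands, and it is why the practical consequence is likely low.

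Three stronger readings are tempting, and the document does not support them.
- A reader might infer that the criterion gives the wrong decision for every participant. That is true only of the literal text. The article reports 6 participants enrolled as of December 2023 and no eligibility problem. This does not prove how the item was applied, but nothing shows misapplication.
- A reader might infer that this is the trial's only safeguard against general medical unfitness. It is not, given the fitness criteria listed above. Nor should the drug's risks be overstated: the article gives suicidal ideation or behavior as 0.2% and rare, and describes Schedule V drugs as having the lowest potential for misuse.
- A reader might infer that checklist answers are reversed at the sites. Study Measurements describes forms completed before enrolment to confirm eligibility, but those forms are not shown, and a journal article condenses a fuller protocol. Whether they carry the 'No' is unknown.

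The reply does not remove the error itself. The criterion is printed here, in current text, and is wrong as printed. The point is about what the article states, not about something it leaves to another document.

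**Conclusion.** The point holds as a minor drafting error. The last exclusion item, taken with the rule that no exclusion criterion may be met, says the reverse of what it evidently means, and it is the only item that names psychiatric illness or substance abuse. Nobody appears to have chosen this; it is a slip of wording and not a design decision.

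The judgement of low consequence assumes that sites read the item by its intent. The number of people affected cannot be derived from the document and may well be zero. With cohorts of 3, one toxicity separates escalating (0 events) from staying (1 event) in Table 1, so a reader might infer that a wrongly admitted participant has altered or will alter a dose decision. The document gives no evidence that anyone was wrongly admitted, and the point does not rest on that.

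**What to change.** Make the wording agree with the list in which it stands. Either delete 'No' from the last item of Textbox 5, or move the sentence unchanged to Textbox 4; the decisions are the same. Then confirm that the full protocol and the eligibility form have the same polarity. If either carries the 'No', check how the item was answered for participants already enrolled.

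The cost is one word, or one moved sentence, plus a look at the form. No calculation, boundary or analysis has to be redone.

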### Objectives and End Point

Our primary objectives are to (1) evaluate the safety, tolerability, and DLT of lacosamide in combination with opioids in patients with CP and (2) assess the feasibility of the performance of a pilot study of adding lacosamide to opioid therapy in patients with CP. As a secondary, exploratory objective, we will assess the efficacy of adding lacosamide to opioid therapy for the treatment of abdominal pain because of CP. The safety end point includes toxicity and DLT of the combination of lacosamide and opioids, defined as grade 3 or 4 toxicities, according to the National Cancer Institute Common Terminology Criteria for Adverse Events v5.0. Tolerability will be assessed by compliance with the intervention. The participants will be evaluated for completing the 7-day trial. The percentage of participants taking 100%, 75%, 50%, and <50% of the study tablets will be recorded. The feasibility end point will include the recruitment rate (ie, the proportion of eligible patients who agree to participate) and the dropout rate, including a qualitative assessment of barriers to retention. The efficacy end point will be assessed using the Visual Analog Score; Brief Pain Inventory, short form, average score; and the Comprehensive Pain Assessment Tool, short form [36] total score. A 50% decrease in pain scores from baseline at study completion will be deemed clinically meaningful. In addition, opioid use will be evaluated, with a decrease of 25% in pain scores from baseline at study completion, identified as clinically significant.

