### Follow-Up Visit

The first follow-up visit will be completed in person on day 8 and is expected to last for 60 minutes. Subsequently, a follow-up visit will be conducted via telephone on day 21. The protocol for these follow-up visits in described in Textbox 3.

Protocol for follow-up visits.

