In the BOIN design, the number of DLT is the number of patients with at least 1 DLT. When none of the actions (ie, escalation, de-escalation, or elimination) is triggered, the current dose remains unchanged for the next cohort of patients. “N/A” means that a dose cannot be eliminated before treating 3 evaluable patients. After the trial is completed, we will select the MTD based on isotonic regression [38]. This computation is implemented by the “Estimate MTD” tab of the BOIN Design Desktop Program [41]. Notably, each cohort of 3 patients will consist of 3 new patients. Therefore, dose escalation or de-escalation is interpatient (or, more precisely, intercohort), not intrapatient in nature.

Considering the low disease prevalence of CP, including referral bias at academic centers, we chose to avoid the use of eligibility criteria that would narrow the potential recruitment pool. In this phase 1 trial, in which safety, tolerability, and feasibility are the primary outcomes of interest, we propose including all patients with suspected or definitive CP if the above inclusion and exclusion criteria are met. Similarly, although there may be potential variability in patients because of the etiology, duration of CP, or other features of the disease, it is impractical to impose more stringent eligibility criteria during this early phase of the investigation. Doing so would substantially deplete the recruitment pool for this orphan disease and would not be feasible or scientifically justified.

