### Study Visits

A screening visit for eligibility in person or via telephone will occur at 7 to 30 days prior to enrollment. There will be 2 in-person study visits. During study visit 1 on day 0, baseline study assessments and questionnaires will be completed in person. Drug treatment days will then occur from days 1 to 7. During study visit 2 on day 8 (with a 3-day window), following completion of the 7-day drug treatment period, participants will have a face-to-face clinic visit, where similar assessments and questionnaires will be completed, as per the study calendar (Table 2). Participants will return all unused drugs during this visit for disposal and to monitor compliance.

**Table 2 table2:** Study calendar.

		Screening visit, from 7 to 30 days	Enrollment visit, day 0	Treatment days 1-7	Follow-up visit, day 8 (+3-day window)

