### Study Measurements

A site gastroenterologist will review the complete medical history, including medications (particularly opioid use), Eastern Cooperative Oncology Group performance status, physical examination (including vital signs, height, and weight), EKG, and laboratory test results. A site research nurse will collect up to 35 mL of fasting blood using standard protocols. Given the safety or risk protocol of lacosamide and to satisfy inclusion and exclusion criteria, the blood specimens are considered routine safety laboratories and will include electrolytes, glucose, blood urea nitrogen, creatinine, creatinine clearance, calcium, and a hepatic function panel.

The patient, nurse coordinator, and physician case report forms (CRFs) will be completed before study entry. This will be based on a similar CRF currently used in PROCEED. Completion of these forms before enrollment will allow confirmation that the patient is eligible for the study. We will obtain approval from the single-center IRB to share data between protocols with the patients’ consent. An additional CRF will be completed by the nurse coordinator in collaboration with the site-specific principal investigator at the follow-up study visit, documenting all side effects noted during the drug treatment phase according to Common Terminology Criteria for Adverse Events (version 5.0).

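### The DLT definition stops at grade 4, so a death would not enter the Table 1 count, and the day-21 safety call is missing from the study calendar

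*Protocol article*

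**What the plan says.** **DLT definition.** Objectives and End Point describes the safety endpoint as toxicity and "DLT of the combination of lacosamide and opioids, defined as grade 3 or 4 toxicities", graded by CTCAE v5.0. No other section extends this to grade 5 or to death.

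**Use of the count.** The Investigational Plan section says that in the BOIN design "the number of DLT is the number of patients with at least 1 DLT". That number is read against Table 1 to escalate, stay, de-escalate or eliminate a dose.

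**Follow-up.** After the day 8 visit, the Follow-Up Visit section states that "a follow-up visit will be conducted via telephone on day 21". Textbox 3 has patients asked on that call about health problems and about medication taken since day 8. Elsewhere:

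- The section on length of participation treats the in-person day 8 visit as the final one.
- The last column of Table 2 begins "Follow-up visit, day 8 (+3-day window", and none follows it. The last adverse event tick is in that column.
- Study Measurements describes one additional case report form, completed at the follow-up visit, "documenting all side effects noted during the drug treatment phase".

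**The concern.** There are two separate problems.

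1. The definition ends one grade short of the scale it names. On the ordinary CTCAE coding, which the article does not print, death is grade 5. The worst possible outcome then adds nothing to the count that governs dosing. With three patients per decision, one uncounted patient is enough to change the action.

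2. The article describes follow-up for its primary safety endpoint in two ways that do not match. One has a safety contact on day 21; the other ends adverse event assessment at day 8 (+3 days). A site working from Table 2 would find no day-21 assessment, and nothing says whether an event reported on that call belongs to the DLT count.

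At stake are the cohort-by-cohort dose assignments and the final MTD, both of which rest on the DLT count.

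**Working it through.** **Inputs from the article.** "The target DLT rate for MTD is 0.3, and the maximum sample size is 24". Each cohort has three patients. The trial may also end early: "stop the trial if the number of patients treated at the current dose reaches 15".

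**Inputs assumed.** The usual BOIN settings φ1 = 0.6φ and φ2 = 1.4φ, and an elimination cutoff of 0.95. The article states none of these.

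**Reproducing Table 1.** With φ = 0.30, φ1 = 0.18 and φ2 = 0.42:

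- λe = ln[(1−φ1)/(1−φ)] / ln[φ(1−φ1)/(φ1(1−φ))] = ln(0.82/0.70) / ln(0.246/0.126) = 0.2365
- λd = ln[(1−φ)/(1−φ2)] / ln[φ2(1−φ)/(φ(1−φ2))] = ln(0.70/0.58) / ln(0.294/0.174) = 0.3585
- Escalate if DLTs ≤ floor(n·λe); de-escalate if DLTs ≥ ceil(n·λd); eliminate if P(p > 0.30 | Beta(1+y, 1+n−y)) > 0.95 with n ≥ 3.

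At n = 3, floor(0.709) = 0 and ceil(1.076) = 2, and elimination is at 3. All 43 numeric cells of Table 1 are reproduced, so the table itself is sound.

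**Effect of one uncounted death.** The patient who died is taken to have no recorded grade 3 or 4 event; otherwise that patient is counted anyway. The actions come from Table 1.

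| Patients at dose | Other patients with a DLT | Death not counted | Death counted |
|---|---|---|---|
| 3 | 0 | 0/3: escalate | 1/3: stay |
| 3 | 1 | 1/3: stay | 2/3: de-escalate |
| 6 | 1 | 1/6: escalate | 2/6: stay |

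**Follow-up text side by side.** Table 2 ends adverse event assessment at day 8, or day 11 at the latest (8 + 3). The telephone contact is on day 21, 13 days after day 8. The contact is described in the Follow-Up Visit section and Textbox 3 but is absent from Table 2, and the form described in Study Measurements looks back to treatment only.

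**Direction of the effect.** If the true DLT probability is p and a share f of patients with a DLT goes uncounted, the chance of seeing 0/3 is (1 − p(1−f))³. At p = 0.45 it is 0.55³ = 0.166 with f = 0, and 0.64³ = 0.262 with f = 0.20. The count can only fall.

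**Size: illustration only.** Simulated BOIN trials used four doses, cohorts of 3, N = 24, a cap of 15, isotonic MTD selection and 10,000 runs each. The assumed true DLT rates were 0.10/0.30/0.45/0.60.

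| Share uncounted (assumed) | Correct MTD | Dose above MTD |
|---|---|---|
| 0% | 59.5% | 19.2 + 2.0 = 21.2% |
| 10% | 55.4% | 26.3 + 4.8 = 31.1% |
| 20% | 47.7% | 33.4 + 10.3 = 43.7% |

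With only 1–2% uncounted, over four assumed curves with the 0.30 dose at level 2 or 3, selection above the MTD rises by about 0.6 to 2.1 percentage points. The article gives no value for the share.

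**The case against.** The case on the other side is substantial, and much of it stands.

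- **No stated DLT window is contradicted.** A reader might infer that the article gives two conflicting windows. It gives none. A follow-up contact is not a DLT window, and an article may leave the window to the full protocol. If the intended window closes at day 8, later events are not missed DLTs, and the simulated loss does not apply to them. What remains is a mismatch in the schedule.
- **The form is not shown.** A reader might infer that the case report forms have no place for day-21 events. Only one form is described, and the text does not exclude another for the call. Textbox 3 does require the question to be asked, and the article provides for adverse event collection in general.
- **Day 8 as the final visit** may mean the final in-person visit, which is how Drug Dispensing and Compliance puts it. That softens this one conflict but does not put day 21 into Table 2.
- **The grade 5 gap is probably a drafting slip.** Routine escalation after a treatment-related death would require the medical monitors and the DSMB to stay passive, which is unlikely. However, the DSMB route (monthly summaries, quarterly review) is not tied to the Table 1 count, so the written rule still gives the wrong number.
- **The 10% and 20% shares have no source.** This stands in full. Treatment lasts 7 days, with examination, laboratory tests and EKG at day 8, so the share of late or fatal events may be very small. The 0.5% and 0.2% quoted for rare severe effects are incidences, not shares of DLTs, and do not supply it.

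**Conclusion.** Both points hold as matters of text. The DLT definition, read literally, leaves out fatal toxicity; in a first cohort of three this can turn stay into escalate. The day-21 safety contact is in the Follow-Up Visit section but not in Table 2, and the follow-up form as described does not reach it.

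The direction is certain: an uncounted DLT lowers the count and favours escalation. The size is not known. A reader might infer from the simulations that the trial would select too high a dose 10 to 20 percentage points more often. The documents do not support that, because the uncounted share is assumed throughout and may be near zero. Nor do they show that late events will be lost, only that the text does not say what happens to them.

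The conclusion rests on two things: the ordinary coding of death as CTCAE grade 5, and the article's text as printed, since neither the full protocol nor the forms are shown. Table 1 and the sample size are unaffected.

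**What to change.** 1. In Objectives and End Point, define a DLT as a toxicity of grade 3 or higher.
2. Add a day-21 telephone column to Table 2, with its adverse event and medication assessments.
3. Reconcile the section on length of participation, the Follow-Up Visit section with Textbox 3, Study Visits with Table 2, and Study Measurements. The reconciled text should state whether events reported on day 21 belong to the DLT count. That choice is the sponsor's; the passages only need to agree.

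The cost is a word in the definition, one table column and one form entry. There is a delay only if the sponsor's DLT window runs to day 21: 21 − 8 = 13 days, or about two weeks at most per cohort. No boundary or sample size needs recalculating.
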